### Assessments and outcomes

#### Data collection methods

The data from screening, outcome measurements, and economic measurements are collected from patients (patient-reported outcome) and from their caregivers/adult reference persons in tablet questionnaires (screening) or in online questionnaires. Medical record data of the participants are collected by physicians and are administered via the patient registers. The data is linked by a patient code (ID patient) and a hash key, in order to combine the data sources in a pseudonymized manner. The research data are stored on a protected cloud using encryption software. Detailed study management protocols and lists are used to monitor data collection. This allows interruptions and protocol deviations to be detected.

For an overview of instruments at screening, baseline (t0), 6 weeks (t1), 3 months (t2), 6 months (t3), and 12 months post-randomization (t4), see Table 3.

**Table 3 Tab3:**
[figure not shown]
SPIRIT schedule of enrolment, intervention, and assessments

*Notes:* t0 = baseline, t1 = 6 weeks, t2 = 3 months, t3 = 6 months, t4 = 12 months, *PHQ-9* Patient Health Questionnaire, *GAD-7* Generalized Anxiety Disorder Questionnaire, *PHQ-ADS* Patient Health Questionnaire Anxiety and Depression Scale, *CODI* Coping with a Disease, *GSE* General Self-Efficacy Scale, *CATS (7–17)* Child and Adolescent Trauma Screen, *SRGS* Stress-Related Growth Scale, *BSSS* Berlin Social Support Scales, subscale “Actually Received Support”, *CSQ-I* Client Satisfaction Questionnaire adapted to Internet-based interventions, *WAI-SR* Working Alliance Inventory-Short Revised, *BADS* Behavioral Activation for Depression Scale, *ATQ-R* Automatic Thoughts Questionnaire-Revised, *EQ-5D-Y* EuroQol Five-Dimensional Questionnaire-Youth, *SCARED* Screen for Child Anxiety Related Emotional Disorders, *MFQ* Mood and Feelings Questionnaire-Caregiver, *CATS-C-D (7–17)* Child and Adolescent Trauma Screen-Caregiver, *INEP-On* Inventory for recording negative effects of online interventions, *IUES* Internet-Use Expectancies Scale, *BDI-II* Beck Depression Inventory-Revised, *CAMHSRI-DE* Child and Adolescent Mental Health Services Receipt Inventory

^a^Recorded in intervention group only

#### Inclusion criteria and outcome assessments

##### Depression and/or anxiety symptom severity

As part of clinical routine, AYA are screened for symptoms of depression and anxiety. The screening questionnaires are the GAD-7 [45] and the PHQ-9 [46] with a defined cut-off score of ≥ 7 in either of the questionnaires [53].

The German version of the GAD-7 is a self-report anxiety questionnaire. It consists of seven items on a 4-point scale and can be scored from 0 = “not at all” to 3 = “nearly every day”. Good internal consistency (α = .79–.91) [54] and successful usage in adolescents are reported [55].

The German version of the PHQ-9 is administered as a screening inventory to detect depressive symptoms. The PHQ-9 consists of nine items on a 4-point scale with a rating scale ranging from 0 = “not at all” to 3 = “nearly every day”. The computerized version (α = .88) of the PHQ-9 shows an equally high internal consistency as the paper-pencil version (α = .89) [56].

##### Sociodemographic variables

As demographic data, we collect date of birth, gender, relationship status, type of school, grade of school or vocational training, and occupation.

##### Medical variables

The collection of medical data takes place at the time of screening at the respective clinical centre. If the relevant parameters were not collected for screening, the closest examination is used at the time of screening; if two examinations are equally far apart, the previous examination is used, maximum one year away from screening. The following medical data of the participants are collected in the disease-specific registers depending on the chronic somatic condition:
*Type 1 diabetes*. HbA1c, number of severe hypoglycaemia (with and without coma) and diabetic ketoacidosis (DKA) events, continuous subcutaneous insulin infusion (CSII)/intensified conventional therapy (ICT), insulin dose per day, self-monitoring of blood glucose (SMBG), continuous glucose monitoring (CGM)/flash glucose monitoring (FGM), diabetes education, and celiac disease*Cystic fibrosis*. Forced expiratory volume in 1 second (FEV 1), diabetes, pancreatic status, liver cirrhosis, pseudomonas infection, number of exacerbations, number of antibiotic therapies, and allergic bronchopulmonary aspergillosis (ABPA)*Juvenile idiopathic arthritis*. Physician’s global assessment of disease activity (numeric rating scale [NRS] 0–10) [57], active joint count, patient/parent global assessment of overall well-being (NRS), the clinical 10-joint Juvenile Arthritis Disease Activity Score [58], functional status (assessed by the Childhood Health Assessment Questionnaire) [59], C-reactive protein (CrP) and juvenile idiopathic arthritis category (systemic arthritis, persistent oligoarthritis, extended oligoarthritis, negative rheumatoid factor polyarthritis, positive rheumatoid factor polyarthritis, enthesitis-related arthritis, psoriatic arthritis, other arthritis).

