## Methods/design

### Objectives

This trial aims to evaluate the effectiveness and cost-effectiveness of youthCOACH_CD_, a guided iCBT for AYA with type 1 diabetes, cystic fibrosis, or juvenile idiopathic arthritis.

The primary objective is:
To evaluate the short-term effectiveness of iCBT in improving depression and anxiety symptoms, assessed using the Patient Health Questionnaire Anxiety and Depression Scale (PHQ-ADS), at 12 weeks post-randomization (t2) compared to enhanced treatment as usual (TAU+).

Secondary objectives of the study are:
2)To evaluate the middle (t3; 6 months post-randomization) and long-term (t4; 12 months post-randomization) effectiveness of iCBT in improving depression and anxiety symptoms compared to TAU+.3)To evaluate the short (t2), middle (t3), and long-term (t4) effectiveness of iCBT compared to TAU+ in improving (a) health-related quality of life, (b) coping strategies, (c) self-efficacy, (d) stress-related growth, (e) social support, (f) behavioural activation, (g) adjustment and trauma-focused symptoms, and (h) automatic thoughts and also to evaluate the (i) working alliance and (j) intervention satisfaction in the intervention group.4)To examine the cost-effectiveness of iCBT compared to TAU+ over a period of 12 months.5)To evaluate the safety of iCBT by examining potential adverse events compared to TAU+.6)To explore potential moderators and mediators of intervention effects.

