### Study design

This is a two-armed, multicentre parallel randomized controlled trial (RCT) comparing iCBT to TAU+. The intervention group receives iCBT in addition to treatment as usual (TAU). Assessments will take place starting with mental health screening in paediatric units followed by five assessment points over one year: baseline (t0), 6 weeks (t1), 3 months (t2), 6 months (t3), and 12 months (t4) post-randomization. The flow chart of the study design is shown in Fig. 1.

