#### Guidance

The intervention is therapist-guided by e-Coaches, who report semi-standardized feedback after each completed module on the intervention platform to the participant using an e-Coach manual. The e-Coach manual is standardized to guarantee protocol adherence by the e-Coaches. e-Coaches are graduates of a Master’s Degree in Psychology or Pedagogy, who are enrolled in a training program in CBT with children and adolescents, closely supervised by licensed psychotherapists. The feedback content matches the participants’ tasks and is aimed to support adherence to treatment. The feedback also includes positive reinforcement to motivate participants to continue the intervention. For further questions, participants and e-Coaches can communicate via the intervention platform. e-Coaches will also send reminders to participants who do not complete intervention modules at the scheduled time via e-mail and telephone. The weekly schedule for processing a module is set by the participants themselves at the end of the previous module. In order to promote commitment, the intervention is blocked for the participant after three reminders without the participant reacting. For participants who indicate that they wish to continue, youthCOACH_CD_ will be reactivated. Table 2 shows the intervention structure and implementation.

**Table 2 Tab2:** Intervention structure, technical implementations, and support

Intervention structure	
• Seven weekly modules (50-70 min.)	
Implemented elements	
• Guidance by trained and supervised e-Coaches (graduates of a Master’s Degree, who are enrolled in a training program in CBT with children and adolescents)	
• One feedback message per module by e-Coaches	
• Reminders by the e-Coach if the modules are not processed at a date set in advance by the participant to promote adherence	
• Deactivation and reactivation when modules are not processed and three unsuccessful reminders	
• Answers to additional questions from e-Coaches and the study team	
• Tight security procedure for suicidal clues	
• Weekly challenges/ homework	
• Diaries via a mobile app with daily reminders	
• Information given by text and videos	
• Audio guided exercises	
• Patient examples written and presented as audio recordings	
• Metaphors, quizzes and conditional content	
• Modules can be repeated as often as desired	

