## Discussion

The aim of this study is to examine the (cost-)effectiveness of youthCOACH_CD_, an iCBT for AYA with a chronic somatic condition and comorbid depressive and/or anxiety symptoms.

The innovative aspects of the study are the following: (1) youthCOACH_CD_ is implemented directly into routine medical care. As such, the present study will provide important insights for health care policy on how to integrate iCBT into our health care systems. (2) Studies show that AYA between the ages of 12 and 25 spend an average of 22 h a week online with an increasing tendency to communicate, play, or entertain. Four out of five of 12- to 17-year-olds (80.6%) have used the Internet daily in the last 12 months [98]. Only 4.6% of adolescents at this age do not make use of the Internet. The fact that AYA grow up as digital natives could make online use of an intervention well accepted.

Continuing with advantages, the methodical strengths of the study are as follows: (3) The area-wide recruitment via the German patient registers enables a representative sample and facilitates generalization. (4) With a target sample of 212 adolescents, the study will be high-powered (1 – β = .90). (5) In addition to self-report questionnaires, the study also includes caregiver self-reports on their perception of participants’ conditions. This provides further insights into the effectiveness of iCBT. (6) Not only the effectiveness of youthCOACH_CD_, but also undesirable potential adverse events will be investigated in detail in this study. (7) As one of as yet only a few clinical trials on psychological interventions for AYA with chronic somatic conditions and symptoms of depression and anxiety, the present RCT also comprises cost-effectiveness analyses. (8) Finally, in addition to the psychological parameters, medical data are collected, which are linked to each other and thus allow deeper insights into comorbidity.

The study has several possible obstacles and limitations. First, adolescents aged 12 to 16 years need the informed consent of the custodial persons to participate in the study. This legal constraint might lead to a left-skewed age distribution of the study participants. By adjusting the covariate baseline to age, sex, and chronic somatic disease, this possible limitation is taken into account in the statistical analysis.

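### The fallback rule for medical parameters missing at screening admits examinations from after randomisation, so some values standing for entry status may already be affected by the intervention

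*Protocol article*

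**What the plan says.** The Medical variables section sets the intended time point: "The collection of medical data takes place at the time of screening at the respective clinical centre". For parameters missing at that point it gives a fallback, with a tie-break and a limit: "the closest examination is used at the time of screening; if two examinations are equally far apart, the previous examination is used, maximum one year" from screening. The section lists the parameters by condition, among them HbA1c, FEV1, number of exacerbations, physician-rated disease activity, patient or parent global well-being and functional status.

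Study design fixes the order of events: "Assessments will take place starting with mental health screening in paediatric units followed by five assessment points over one year". Those five points start with t0, and the follow-ups are timed from randomisation. Table 2 (Guidance) gives seven weekly modules, and Objectives places t2, the primary time point, 12 weeks after randomisation.

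On use, the Discussion names as a strength that "medical data are collected, which are linked to each other and thus allow deeper insights into comorbidity". Statistical analyses says only that participant characteristics will be described. Effectiveness analysis adjusts for the baseline score, sex, age and chronic somatic condition, and names outcomes and demographic data for the exploratory mediation and moderator analyses.

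**The concern.** A value that describes a participant at entry should come from before randomisation, so that allocation cannot have influenced it. This rule selects on distance from screening and never mentions randomisation. A later examination therefore replaces the missing value whenever it is nearer than the last earlier one.

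The protocol supplies a route by which such a value could be altered. Its Background associates depression and anxiety symptoms with reduced treatment adherence and poorer long-term prognosis, so an intervention that changes symptoms could change HbA1c, exacerbations or disease activity. Patient-reported items such as global well-being are open to this more directly.

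At stake is whether the medical description of the two arms is a true picture at entry, and whether associations between medical and psychological data mix status before treatment with response to it. A difference between arms in such a description could partly be an effect of treatment.

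**Working it through.** **Does the rule really admit later examinations?** Two earlier examinations equally far from screening would fall on the same date. A tie that is settled in favour of the previous examination can therefore arise only if later ones are eligible. Reading the rule as limited to examinations already available at screening would leave the tie-break without a function. The one-year limit could grammatically attach only to the previous examination; later ones would then have no stated limit. The calculation below uses the narrower reading, one year either way.

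The one-year limit is a rule and not a derived figure, so there is no number of the plan's own to reproduce.

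**How much of the forward window lies after randomisation?** Inputs:
- forward window: 365 days (Medical variables);
- programme: 7 modules × 7 days = 49 days (Table 2);
- t2: 12 × 7 = 84 days (Objectives);
- gap g from screening to randomisation: not given, assumed 0 to 56 days.

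Days remaining = 365 − g − d, with d = 0, 49 or 84.

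| g (days) | After randomisation | After 7 modules | After t2 |
|---|---|---|---|
| 0 | 365 | 316 | 281 |
| 14 | 351 | 302 | 267 |
| 28 | 337 | 288 | 253 |
| 56 | 309 | 260 | 225 |

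These are outer limits. A value from late in the window is used only if no nearer examination exists on either side.

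**How often would a substituted value be affected?** The protocol gives neither visit spacing nor the gap, so this is an illustration. Assume visits every L days, each recording the parameter, and screening at a random point between two of them. The next visit is nearer when it lies less than L/2 ahead. It is also more than g + d days ahead with probability

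(L/2 − g − d) / L = 0.5 − (g + d)/L, or 0 if this is negative.

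For L = 90, g = 28, d = 0: 0.5 − 28/90 = 0.19. For L = 365, g = 0, d = 49: 0.5 − 49/365 = 0.37.

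| L (days) | After randomisation, g = 0 to 28 | After 7 modules, g = 0 to 28 |
|---|---|---|
| 90 | 50% to 19% | 0% |
| 180 | 50% to 34% | 23% to 7% |
| 365 | 50% to 42% | 37% to 29% |

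The denominator is substituted values only, not all participants. The rate of missing parameters at screening is not stated.

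**Which stated analyses use these values?** The primary model contains the baseline PHQ-ADS score, sex, age and chronic somatic condition. The last is the diagnosis, which is also the stratification factor, not a laboratory or disease-activity value. Secondary outcomes are analysed in the same way. None of these terms comes from the fallback rule, and neither do the sample size inputs.

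**The case against.** The strongest reply is that no treatment-effect analysis in the protocol uses these values. That stands. A reader might infer that the primary result is biased, or that the planned moderator and subgroup analyses condition on post-treatment variables. The documents do not support either. The models adjust for none of these parameters, and the moderator analyses name only outcomes and demographic data, which the protocol lists separately from medical variables. The open wording of the sixth objective leaves later use possible but does not plan it.

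Second, the protocol ties these values to screening and never calls them baseline, and it does not say that later values lose their dates. This also stands. The point is that the values serve as status at screening, not that the protocol mislabels them.

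Third, for describing association with symptoms at screening, a value close in time may be more informative than one nearly a year old. That is a fair argument for proximity. It does not justify crossing randomisation without separating those values.

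Fourth, the size is uncertain. A reader might infer that about half of substituted values are post-randomisation. Half is the share after screening under the random-timing assumption, and becomes the share after randomisation only when the gap is zero. If screening is itself one of a series of exactly equally spaced visits, the neighbouring visits tie, the earlier is taken and the share is 0%. Any irregularity breaks the tie, and the later visit can then be the nearer. This shows that the share depends on assumed visit timing; it does not show that the rule is safe. Nor is there a 12-week treatment period to count against: the programme is seven weekly modules, and 12 weeks is the t2 assessment.

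Finally, some listed items (arthritis category, celiac disease, pancreatic status, liver cirrhosis) are unlikely to be moved by a psychological programme. The point concerns the changeable ones.

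**Conclusion.** The rule as written allows an examination after randomisation to stand for medical status at screening. That conclusion rests on the text alone, through the tie-break and the order of screening and randomisation.

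The consequence is limited: the effect models, N and power are unaffected. Exposed are the description of participants' medical status, the comorbidity linkage, and any later use of the values as covariates or moderators.

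The illustrative ranges, 19% to 50% of substituted values after randomisation and 0% to 37% after the modules, hold only for visits every 90 to 365 days, a gap of 0 to 28 days, random timing of screening and modules completed on the weekly schedule. They show that the problem need not be rare among substituted values; they do not estimate its frequency in this trial. It is a modest point, but worth correcting because the faulty rule is explicit.

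**What to change.** Replace the fallback with: use the most recent examination on or before the date of randomisation, at most one year before screening; if there is none, treat the value as missing. The multiple imputation already planned under Statistical analyses can then be applied, within condition where a parameter exists for one condition only. Keep later registry values under their own examination dates as follow-up data.

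Under this rule no substituted value can come from after randomisation: 0 days of the window, against 309 to 365 days now. It uses registry data and needs no new patient contact, and sample size and power do not change. The downside is somewhat older or more missing values. The extraction rule would have to be changed consistently across three registries; the protocol gives no basis for costing that work.

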### Outcome measurements

#### Primary outcome: depressive and anxiety symptom severity

The primary outcome is the combined depressive and anxiety symptom severity at t2, assessed with the PHQ-ADS [50]. Depression and anxiety symptoms at all other assessments will be considered as secondary outcomes. PHQ-ADS is the combined sum score of the questionnaires GAD-7 and PHQ-9 as a composite measure of depression and anxiety, with good internal consistency (α = .88 to .92) [50].

#### Secondary outcomes

##### Coping with chronic health conditions

The Coping with a Disease (CODI) questionnaire for children and adolescents with chronic health conditions [60] is a self-report questionnaire to assess coping strategies of children and adolescents (ages ranging from 8 to 18 years) with chronic health conditions. The CODI questionnaire includes 29 items on a 5-point scale with a rating scale ranging from 1 = “never” to 4 = “all the time”. The questionnaire shows an internal consistency depending on the domain between α = .69 and α = .83 [60].

##### General perceived self-efficacy

General perceived self-efficacy represents a personal coping resource with predictive value for well-being and a constructive coping with life [61, 62]. It serves the personal assessment of one’s own competence, generally to cope with difficulties and barriers in daily life successfully. The reported psychometric parameters of the General Self-Efficacy Scale (GSE) are satisfactory. The internal consistency ranges from α = .80 to .90 for various German samples [63]. The 10 items of the GSE can be rated on a 4-point scale from 1 = “is not true” to 4 = “is absolutely right”.

##### Traumatic experiences and personal growth

The symptom list of the Child and Adolescent Trauma Screen (CATS) for ages 7–17 years is used to observe the changes within treatment in psychological stress caused by traumatic events due to a chronic somatic condition [64]. The questions about trauma-specific symptoms are introduced by the request that the AYA refer to the currently most stressful event with regard to their chronic condition and describe it briefly. The severity of the symptom scale can be rated from 0 = “never” to 3 = “almost always”. Limitations of the functional level in different areas of life are also assessed. In all three countries where the scale has been validated (the USA, Germany, Norway), the 20-item symptom score of the self-report proved good to excellent reliability between α = .88 and α = .94 [64].

The Stress-Related Growth Scale (SRGS) serves to observe the changes that occur during treatment in relation to the individual development caused by the chronic disease. The construction of the SRGS [65] followed the theoretical concept of coping resources of Schaefer and Moos [66]. The present study uses the 15-item short form (α = .89) adapted to the specific population of AYA with a chronic somatic disorder. The items are answered on a 3-point scale with the values 0 = “not at all”, 1 = “something”, and 2 = “a lot” [67].

